## Introduction

Chronic kidney disease (CKD) has become an increasing global health problem, partly due to the continuously rising incidences of diabetes mellitus, obesity, and hypertension [1]. It is estimated that 8 to 16% of the world’s population suffer from CKD, and the rate is even higher in people with DM2, where cross-sectional studies report percentages of roughly 25% [2]. Ninety-five percent of people with early CKD are unaware of their disease [3]. However, early prediction of the continuous decline in kidney function could provide an additional resource for personalized preventative care [4]. Personalized risk assessment based on large study cohorts could therefore offer several potential benefits to the preventive care for people with DM2 such as early detection followed by monitoring to guide treatment and potentially slow the progression of the decline of kidney function as expressed by the estimated glomerular filtration rate (eGFR) [4]. Despite the accumulated knowledge with regard to CKD nowadays, identifying individuals at high risk for fast disease progression has proven to be challenging because longitudinal eGFR slopes not only vary between patients (inter-patient variability), but eGFR measurements also fluctuate within each patient over time (intra-patient variability) [5].

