Nevertheless, several prediction models for the progression of renal function decline have previously been developed in various populations. It is of note that the models which were developed in studies from the last decade may no longer be applicable nowadays, because the new treatment classes of SGLT2-blocker and mineralocorticoid receptor antagonists have dramatically changed the course of CKD progression [6–8]. In addition, existing predictive models have mainly considered hard renal endpoints such as incidence or end-stage renal failure [9, 10]. Studies focused on renal function have mainly considered simplifications of the longitudinal eGFR trajectory by dichotomization of the expected eGFR slope. For instance, Subasi et al. [11] conducted a pilot study based on a randomized double-blinded treatment trial, the African American Study of Kidney Disease and Hypertension (AASK), in order to predict the rate of kidney function decline. The least-squares slopes of GFR decline from the 6-month time point until censoring were used to define rapid (i.e., an absolute slope < 3mL/min/1.73m^2^/year) and slow (i.e., absolute slope in between 1 and 3mL/min/1.73m^2^/year) progressors for this study. Similarly, Vigil et al. [12] aimed towards the identification of predictors of a rapid decline of renal function defined as an annual eGFR loss > 4 mL/min/1.73m^2^. However, covariates considered for selection in this analysis were chosen on the basis of their significance in univariable analysis (or by their clinical or biological relevance). Despite its popular use for data reduction, univariable prefiltering has been shown to lead to suboptimal or biased selection results [13]. Pena et al. [14] showed that a panel of novel biomarkers improves the prediction of renal function decline in people with DM2. In contrast to the other mentioned studies, renal function decline was not dichotomized. The eGFR slope was estimated using linear regression and then constituted the outcome of interest in its continuous form. People with an observed eGFR decline larger than −3mL/min/1.73m^2^ were considered stable, all others were considered to be rapid progressors in terms of kidney function decline. Then, a person’s risk was assessed by dichotomizing the observed decline in these two groups and comparing it with the predicted probabilities of eGFR decline. The threshold of −3mL/min/1.73m^2^ was selected based on literature, which however included older studies without the current state-of-the-art therapy of diabetic kidney disease, where a GFR loss of only 1mL/min//1.73m^2^/year is standard [14–17]. Furthermore, molecular data in regular clinical care is usually not easily available and no validated reference values exist for these markers.

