### Target population

The following inclusion criteria will be applied to the individuals from the PROVALID, GCKD, and DIACORE studies for the development and validation of the prediction model in this work:
Caucasian ethnicityPresence of DM2 at baselineeGFR > 30 mL/min/1.73m^2^ at baselineAged 18–75 years at baselineAt least three visits with recorded serum creatinine measurements (including baseline)At least 2 years of follow-up

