### Study outcome

The primary outcome of interest for the study is the annual decline in renal function, derived through the use of at least 3 follow-up measurements of eGFR. The eGFR values will be calculated by the equation of the Chronic Kidney Disease Epidemiology Collaboration (CKD-EPI) using the patient’s race, sex, age, and serum creatinine level [21].

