where $$ {\hat{\mathrm{y}}}_{\mathrm{j}0} $$ denotes the estimated baseline value from the fixed effects, $$ {\sigma}_{\epsilon}^2 $$ denotes the variance of the random error and $$ {\sigma}_0^2 $$ the variance of the random intercept in the covariance matrix of the random coefficients *G*. The estimated random slope $$ {\hat{b}}_{1j} $$ for the new individual can be obtained by
3$$ {\hat{\mathrm{b}}}_{1\mathrm{j}}=\frac{\upsigma_{01}{\hat{\mathrm{b}}}_{0\mathrm{j}}}{\upsigma_0^2} $$

In actual predictions, estimates are plugged in for $$ {\sigma}_o^2 $$, σ_01_, and $$ {\upsigma}_{\upvarepsilon}^2 $$. The preliminary prediction $$ {\hat{y}}_{jt} $$ for the new subject *j* at time *t* can then be updated by
4$$ {\overset{\sim }{\mathrm{y}}}_{\mathrm{jt}}={\hat{\mathrm{y}}}_{\mathrm{jt}}+{\hat{\mathrm{b}}}_{0\mathrm{j}}+\mathrm{t}{\hat{\mathrm{b}}}_{1\mathrm{j}} $$

The predicted eGFR slope for a new individual, combining fixed and random effects, is finally given by $$ d\tilde{y}_{j}:= d{\overset{\sim }{\mathrm{y}}}_{\mathrm{j}\mathrm{t}}/ dt={\hat{\upbeta}}_2+{\hat{\upbeta}}_3{\mathrm{X}}_{\mathrm{j}}+{\hat{\mathrm{b}}}_{1\mathrm{j}} $$ with $$ {\overset{\sim }{V}}_j $$ expressing the variance of the predicted eGFR slope of individual *j*.

Given a correct model specification, the probability of progression can then be obtained by a normal approximation:
5$$ \Pr \left(\mathrm{Z}={\mathrm{z}}_{\mathrm{j}}\right)=1-\Phi \left(\frac{{\mathrm{C}}_{\mathrm{p}}-d{\overset{\sim }{\mathrm{y}}}_{\mathrm{j}}}{\sqrt{{\overset{\sim }{V}}_j}}\right) $$

where *z*_*j*_, *j* ∈ {1, 2} denotes the membership of belonging to one of the two progression groups: rapid and stable progression, and Φ(x) the standard normal distribution function at *x*. *C*_*p*_ is the corresponding subject-specific cutpoint for defining progression of kidney decline, which will be set to −3mL/min/1.73m^2^/year at default or can be specified by the intended user in the web application (see Section "Web implementation") [14–16]. Now, one can compute the expected probability of belonging to either of the eGFR progression groups given a patient’s baseline characteristics and the baseline eGFR.

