### Model evaluation, performance, and external validation

An analysis of the conditional residuals will be conducted to check correct model specification, e.g., normality, linearity, and homoscedasticity of the error terms. Next, the importance of each independent variable will also be evaluated by the drop in the adjusted *R*^2^, i.e., the loss in estimated explained variation when the respective predictor is removed from the model.

The performance of the prediction model will be evaluated by an internal-external validation procedure to obtain a reliable assessment of its generalizability of prediction to unseen data [29]. The unit for the non-random data splitting will be the six countries within the PROVALID and GCKD studies (GCKD: Germany; PROVALID: Austria, Hungary, Netherlands, Poland, and Scotland) such that for each iteration, one regional group with its study participants are withheld from model training and then used for testing.

The prediction performance will further be assessed through:
Discrimination in terms of Kendall-tau-b concordance correlation coefficients at each time point, i.e., the concordance of the predicted eGFR values at time *t* obtained by Eq. (4) and the actual observed eGFR in each pair of patientsCalibration in terms of the slope of the calibration curve by
I.Regressing the predicted eGFR on the actual eGFR values at each time pointII.Plotting the estimated mean risk for fast progression per decile against the observed ratio of fast progression within each risk decileExplained variation in terms of adjusted *R*^2^, i.e., the proportion of explained variability in the outcome by the independent variables

The external validity of the model will be examined by applying the final prediction model to the DIACORE study cohort and evaluating the three performance measures outlined above.

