## Discussion

In this study, we have described the protocol for the planned development and validation of a new clinical prediction model for the decline of renal function in Caucasian people with DM2 to aid decision-making in clinical care. Our methodological approach will be based on a multivariable linear mixed model able to account for the dependence of clinical parameters per subject over time and for the similarity of individuals within the same country. Previous studies have employed risk prediction based on (multinomial) logistic regression models for which as a dependent variable the dichotomized eGFR slope was used, after estimation by least squares using the repeated measurements and then partitioning at arbitrary cutpoints. Each eGFR strata then covers different intervals on the eGFR slope spectrum and is supposedly indicative of varying severity of the progression of renal function loss. However, this approach suffers from several shortcomings. First, individual eGFR slopes can only be estimated very inaccurately, as only very few data points at non-equidistant time points are available for each patient [5]. Moreover, the categorization of the resulting eGFR slopes adds another layer of possible bias as it leads to subjects close on the continuous spectrum but on the opposite sides of the cutpoint being characterized as different [31]. By contrast, our approach avoids the issues associated with the imprecise estimation of slopes and inappropriate dichotomization prior to model development and takes the observed data fully into consideration when estimating the parameters of the model. In addition, we include the baseline measurements of eGFR into the outcome vector of an individual, as it is subject to the same measurement error as later eGFR measurements. In this way, these baseline measurements contribute to a more precise estimation of the error variance. Nevertheless, available eGFR measurements at the time of prediction (application of the model) can still be incorporated in our approach to optimize the predicted eGFR trajectory. In addition, the clustered data structure due to the two multicentre cohorts (GCKD and PROVALID) for model training will be taken into account by including an additional random intercept for the country in contrast to existing models. Therefore, the potential heterogeneity of model performance across the countries, which are distinct between GCKD and PROVALID, is prevented and hence, the generalizability to unseen individuals is improved.

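### The risk-decile calibration plot compares a probability about the underlying eGFR slope with an observed rate built from a few noisy eGFR values, so a correct model can look miscalibrated, severely so with short follow-up

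*Protocol article*

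**What the plan says.** The section on model evaluation, performance and external validation lists two calibration checks. The first regresses predicted on actual eGFR at each time point. The second is "Plotting the estimated mean risk for fast progression per decile against the observed ratio of fast progression within each risk" decile. Both apply to internal-external validation and to external validation in DIACORE.

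The predicted risk is Eq. (5) in the section on prediction model development: a normal probability built from the predicted slope, a term "expressing the variance of the predicted eGFR slope of individual" j, and a cutpoint "which will be set to −3mL/min/1.73m^2^/year at default".

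The protocol does not say how a patient is classed as an observed fast progressor. The nearest definition is under Study outcome, where annual decline is "derived through the use of at least 3 follow-up measurements of eGFR". Eligibility under Target population needs three creatinine visits including baseline and "At least 2 years of follow-up". The Discussion says that "individual eGFR slopes can only be estimated very inaccurately, as only very few data points at non-equidistant time points are available for each patient", and counts categorising such slopes as a further source of possible bias.

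**The concern.** An underlying slope is never observed. Any observed proportion of fast progressors has to be scored from a handful of fluctuating eGFR values, and the scoring error is not part of Eq. (5). The two axes of the plot therefore carry different quantities, and a gap between them need not mean that the model is wrong.

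The eGFR-level check assesses predicted values, not risks. The decile plot is therefore the only planned direct check of the rapid-decline probability. That probability feeds the relative risk and the risk assessment in the web application, which is offered to clinicians and patients. If the plot mixes model error with scoring error, its users cannot tell how far to trust the displayed probability.

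**Working it through.** **The plan's own figure.** The protocol states no figure for this plot, so there is none to reproduce.

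**Inputs from the protocol.** Cutpoint −3 mL/min/1.73m² per year; minimum of three visits and 2 years; PROVALID followed for at least 5 years; DIACORE visits bi-yearly for at least 10 years (read here as every two years). The Introduction describes modern care as a setting "where a GFR loss of only 1mL/min//1.73m^2^/year is standard", hence a mean slope of −1.

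**Assumptions, because the protocol gives no variance components.** True slopes are normal with SD 1.5. Within-patient residual SD σε is 3 to 7. The variance in Eq. (5) is that of the true slope given the predictors. As printed, Eq. (5) gives the probability of a slope above the cutpoint; I use its complement for rapid decline.

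**Step 1: true rate.** Φ((−3 + 1)/1.5) = Φ(−1.333) = 9.1%.

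**Step 2: rate scored from least-squares slopes.** Such a slope has extra variance σε²/Sxx, with Sxx = Σ(t − t̄)². The observed rate is Φ(−2/√(1.5² + σε²/Sxx)). Example with σε = 5 and visits at 0, 2 and 4 years: Sxx = 8, variance 2.25 + 25/8 = 5.375, SD 2.318, rate Φ(−0.863) = 19.4%.

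| Visits (years) | Sxx | σε = 3 | σε = 5 | σε = 7 |
|---|---|---|---|---|
| 0, 1, 2 | 2 | 22.1% | 30.1% | 35.0% |
| 0, 2, 4 | 8 | 13.8% | 19.4% | 24.5% |
| 0 to 5, annual | 17.5 | 11.5% | 14.9% | 18.7% |
| 0 to 10, two-yearly | 70 | 9.7% | 10.8% | 12.2% |

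The true rate is 9.1% in every cell. If bi-yearly meant half-yearly, five visits over 2 years give Sxx = 2.5 and, at σε = 5, a slope standard error of 5/√2.5 = 3.2 per year, so short follow-up would still be a problem.

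**Step 3: by decile for a correct model.** Split the slope SD of 1.5 into a predictable part of 0.8 and a remainder of 1.27 (√(2.25 − 0.64)), and take σε = 6.
- Visits 0, 2, 4: lowest decile 0.4% predicted against 8.6% observed; fifth 4.9% against 19.8%; seventh 9.2% against 24.7%; top 32.3% against 40.5%. The largest absolute gap is in the seventh decile (15.5 points); the largest ratio is in the lowest.
- Two-yearly to 10 years: the largest gap is about 3 points.

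**Step 4: the other natural scoring rule.** A separate simulation applied Eqs. (2) to (4) with mean slope −1, predictable SD 0.7, remaining slope SD 1.5, σε = 5, random-intercept SD 15 and zero intercept–slope correlation. Mean predicted risk was about 11.4%.

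| Visits (years) | Observed, least squares | Observed, shrunken slopes | Logit calibration slope, least squares | Logit calibration slope, shrunken |
|---|---|---|---|---|
| 0, 1, 2 | 30.3% | 1.5% | 0.33 | 3.40 |
| 0, 2, 4 | 20.4% | 4.8% | 0.57 | 1.89 |
| 0 to 5, annual | 16.4% | 7.3% | 0.73 | 1.40 |
| 0 to 10, two-yearly | 12.7% | 9.9% | 0.90 | 1.09 |

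Scored against the true slope, the same model had calibration slopes of 0.99 to 1.01.

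**Step 5: sensitivity.** The grid covered mean slope −1 or −2, predictable SD 0.7 to 1.0, remaining SD 1.0 to 2.0 and σε of 3, 5 or 8. The least-squares calibration slope of a correct model ran from 0.12 to 0.67 for three visits over 2 years, and from 0.61 to 1.00 for two-yearly visits to 10 years. The largest decile gaps were 9–34 and 0.5–8 points respectively.

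**The case against.** The strongest reply is that the protocol never says patients will be classed by least-squares slopes, and that a journal article may leave that rule to a fuller plan. This stands as far as direction goes: a reader might infer that the plot will always show under-prediction, but shrunken slopes would show the reverse. It does not remove the point, because both natural rules mismatch Eq. (5), so naming either one would not be enough.

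The second reply is follow-up. DIACORE plans at least 10 years and GCKD runs up to 10, and there the distortion is small. That also stands, and it rules out saying that any correct model must look badly miscalibrated. But eligibility asks for only 2 years, the follow-up actually analysed is not stated, and PROVALID, with at least 5 years, supplies five of the six internal-external folds.

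Third, the protocol objects to categorised slopes before model development, while here they serve only for evaluation. That is fair: this is not a flat contradiction. The imprecision the Discussion describes applies all the same.

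Fourth, the eGFR-level calibration and the residual checks test the same trajectory model without slope classes. They do, but they do not test the probability directly.

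Three further inferences are tempting and unsupported. That the plot cannot tell a good model from a bad one was not computed, and observed rates still rise steeply across deciles. That it would lead to a harmful upward recalibration has no footing, since none is planned. That the error is largest in the low-risk deciles is true only as a ratio.

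**Conclusion.** The point holds in limited form. The risk-decile plot sets a probability about an underlying slope against a rate scored from noisy measurements, and a correct model can therefore look miscalibrated. Under the stated assumptions, a true rate of 9.1% would be scored by least squares at roughly two and a half to four times that value at the eligibility minimum, and at no more than about 1.3 times with two-yearly visits to 10 years.

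The mismatch follows from the protocol's own definitions. Its size rests on variance components that the protocol does not give, and its direction on a scoring rule that it does not state. The plan should be changed on this point, since this is the only direct check of a probability that users of the web tool will see.

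**What to change.** State how observed fast progression is scored, and plot it against the model probability of that same event. If scoring uses the least-squares slope at the patient's own visit times (baseline at t = 0), the predictive variance given baseline eGFR, in the protocol's notation, is σ1² + σε²/Sxx − c²/(σ0² + σε²), with c = σ01 − σε²·t̄/Sxx. The predicted mean is the fixed-effect slope plus c/(σ0² + σε²) times the baseline residual. The c term is needed because the baseline value enters both the prediction and the scored slope.

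In the Step 4 simulation this restored calibration in all four schedules: calibration slopes were 1.00 to 1.01. For three visits over 2 years, mean predicted risk was 30.4% against 30.3% observed, with 15.4% against 15.5% in the lowest decile and 48.4% against 47.9% in the top one.

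Alternatively, calibrate the probability that eGFR at set times falls below a threshold, using the predictive distribution with residual error included.

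The cost is a few lines of validation code and no new data. The downside is that the plot then checks the probability of the measured event, and only indirectly the true-slope probability that the web tool displays; the report should say so.

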### Model presentation

Reporting of the model development and the final prediction model will adhere to the Transparent Reporting of a Multivariable Prediction Model for Individual Prognosis or Diagnosis (TRIPOD) statement, a checklist of items that ought to be reported when publishing a statistical prediction model [30]. The results of this analysis will be published in a peer-review journal. In particular, the final regression model will be presented using regression coefficients and 95% confidence intervals. Further, model reporting will include the covariance matrix of the random effects, the error variance, and the regression formula to allow independent application and validation of the model. Visualizations of results will be generated to improve model literacy for non-statistical readers and users of the web-based calculator.

### Web implementation

The externally validated model will be implemented as an interactive prediction calculator, made available online as a web application to support clinical care and medical decision-making with regard to prevention and treatment of chronic kidney function decline in people with DM2. The interactive web application will be created with the help of the R development framework *shiny* to allow for individual input and the computation of patient-specific predictions given their baseline characteristics. The web application will offer two user interfaces to choose from:
A patient interface with a web layout consisting of limited input controls (i.e., text fields or checkboxes to enter age, sex, eGFR, and UACR)A clinician interface with a layout featuring input controls for all predictors (i.e., includes laboratory measurements, medication) within the validated prediction model

Both interfaces will be based on the same prediction model formula, with predictors that are excluded from the web layout in the patient interface being fixed as the average value for the continuous variables and the value with the highest relative frequency for the categorical variables. As a result, the use of the model should not only be made available to clinical staff but also to patients themselves.

The output of the web application will contain the following components:
The eGFR value estimated by the model in 1–5 years with 95% model-based prediction intervalsThe predicted eGFR decline per year with 95% model-based prediction intervalThe proportion of people with higher predicted eGFR lossThe relative risk, i.e., the probability for a rapid eGFR decline for the predicted interval divided by the probability of a rapid eGFR decline for a person with equal age, sex, and baseline eGFR, but most favorable values of all other clinical baseline variables (with rapid decline specified by the intended user)A visual representation of the results:The visual communication of the results to the user will illustrate the estimated eGFR decline in the context of the distribution of predicted eGFR declines in the development cohort. In addition, a figure will be generated that shows the predicted trajectory of eGFR over the next 5 years with a 95% prediction interval.

A further option will be the possibility of risk assessment of rapid and stable eGFR decline. However, the choice of cutpoint selection for the categorization will be left to the user of the web-based implementation, in that the user can freely enter a suitable cutpoint for the eGFR classification into rapid and stable progression, whereby the risk of the new individual is estimated. By default, the eGFR cutpoint will be set to −3ml/min/1.73m^2^.

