### Sample size

Overall, 13 predictors will be included in the prediction model. Guidelines regarding the minimum required sample size for the development of a new multivariable prediction model have been recently proposed by Riley et al. [22]. Using the accompanying R package “pmsampsize” with an assumed average value for eGFR of 78.4mL/min/1.73m^2^ and a standard deviation of 21.4 mL/min/1.73m^2^ [23] in the population, an anticipated *R*^2^ of the model of 0.3 [24] and a shrinkage factor of 0.9, the minimum sample size aimed at minimization of overfit and the precise estimation of the parameters of a prediction model with 13 predictors is 271. Further, since regularization is not taken into consideration in model development due to the abundance of data relative to the number of predictors, the computation with a shrinkage parameter of 0.99 results in a sample size of 3048 required subjects. However, a much larger *R*^2^ is expected, which is why a minimum sample size of 1569 is required for a *R*^2^ of 0.5 and 903 participants for 0.7, respectively. Nevertheless, the development cohort will comprise around 5800 subjects and thus will exceed the minimum required sample size by far.

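### The patient web interface runs the full model with ten of 13 predictors fixed at means or modes, and no validation step tests that version

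*Protocol article*

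**What the plan says.** The Sample size section states: "Overall, 13 predictors will be included in the prediction model". Clinical predictor variables lists them: age, sex, BMI, smoking, HbA1c, UACR, three medication classes, systolic and diastolic pressure, hemoglobin and cholesterol.

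Under Web implementation, the patient interface has only "text fields or checkboxes to enter age, sex, eGFR, and UACR". On the model behind it, the section says: "Both interfaces will be based on the same prediction model formula". For inputs that the patient does not see, it describes "predictors that are excluded from the web layout in the patient interface being fixed as the average value for the continuous variables". Hidden categorical predictors instead take "the value with the highest relative frequency for the categorical variables". The web application's listed outputs are model-based 95% prediction intervals for eGFR and for the yearly decline, the share of people with a larger predicted loss, and a relative risk of rapid decline. The section opens with: "The externally validated model will be implemented as an interactive prediction calculator".

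Under Model evaluation, performance, and external validation, performance is assessed by leaving out one country at a time. External validity is then assessed by "applying the final prediction model to the DIACORE study cohort and evaluating the three performance measures outlined above". Neither step sets any input to a mean or a mode.

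**The concern.** The patient interface is a different prediction rule from the one that is validated. It uses the same coefficients but treats ten unknown inputs as known. This can go wrong in three ways, each of which needs at least one hidden predictor with an effect on the slope:

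- A mode is not an expected value. Giving everyone the majority category shifts every predicted slope by the same amount.
- An overall mean ignores what age, sex and UACR say about the hidden predictors. If they are correlated, the spread of predicted slopes is wrong.
- The slope variance in the interval and in Eq. (5) is that of a model in which all predictors are known. It has no term for the values the patient did not enter.

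Such effects are part of the plan. The abstract says interactions of the clinical variables with time will be fitted. Prediction model development says clinically relevant ones will be kept where AIC improves.

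At stake is the version patients would use themselves. Performance figures obtained with all 13 inputs cannot be carried over to it.

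**Working it through.** **Count.** Of the 13 predictors, the patient enters three (age, sex, UACR). Baseline eGFR enters through Eqs. (2)–(4). Hidden: 13 − 3 = 10, of which six are continuous (BMI, HbA1c, two blood pressures, hemoglobin, cholesterol) and four binary (smoking, three medication classes).

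**No planned figure to reproduce.** The article gives no performance figure for the patient interface, and no coefficients, prevalences, correlations or variance components. Everything below is illustrative. Slopes are in mL/min/1.73m²/year.

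**1. Shift from the mode.** For a hidden binary with time effect b, predicted minus expected slope = b × (mode − prevalence).
- b = 0.4, prevalence 71%: 0.4 × (1 − 0.71) = 0.12. A simulation of 400,000 people with these inputs gave 0.10.
- b = 0.4, prevalence 90%: 0.4 × 0.10 = 0.04.
- b = 0.5, prevalence 60%: 0.5 × 0.40 = 0.20, which is 20% of the yearly loss of 1 that the Introduction calls standard under current therapy.

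The sign follows the sign of b and which category is the mode. Several binaries can add or cancel.

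**2. Calibration slope from the overall mean.** Let an entered predictor have slope effect s per SD, and a hidden one effect h per SD with correlation r. Leaving baseline eGFR aside, calibration slope ≈ (s + h·r)/s. With s = 0.8, h = 0.6:
- r = +0.3: (0.8 + 0.18)/0.8 = 1.23
- r = −0.3: (0.8 − 0.18)/0.8 = 0.78

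The simulation, which includes baseline eGFR through Eqs. (2)–(4), gives 1.23 and 0.82.

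**3. Missing variance.** With random-slope SD 1.5, h = 0.6, r = 0.3 and the 60% binary with b = 0.5, and ignoring the small gain from baseline eGFR:
- omitted variance = 0.36 × (1 − 0.09) + 0.25 × 0.6 × 0.4 = 0.328 + 0.060 = 0.388
- required widening = √(1 + 0.388/2.25) = 1.083, about 8%
- coverage of the unwidened interval = 2Φ(1.96/1.083) − 1 = 93.0%; the simulation, which also carries the 0.2 shift, gives 92.8%.

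**4. Simulated range.** Assumed: intercept SD 15, residual SD 6, random-slope SD 1.5, mean slope −1, s = 0.8, one hidden continuous index, and one hidden binary (60%, b = 0.5). Full input gives bias 0, calibration slope 1.0 and coverage 95%. Patient input gives bias +0.2 in each row below.

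| h per SD | Calibration slope, r = +0.3 | Calibration slope, r = −0.3 | Slope-interval coverage | 5-year eGFR interval coverage | Widening needed |
|---|---|---|---|---|---|
| 0.3 | 1.11 | 0.91 | 94.1% | 94.4% | 3% |
| 0.6 | 1.23 | 0.82 | about 93% | 93.7% | 8% |
| 0.9 | 1.35 | 0.73 | 90.4% | about 92.5% | 17% |

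The mean predicted risk of a slope below −3 is about 10%, against a true 12 to 17%. With r = 0 the calibration slope is 1.02 to 1.04. With no hidden time effect, coverage stays at 95% and calibration slope at 0.98 to 1.01.

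**5. Hidden effects of 0.4 per year.** Separate simulations with r of about ±0.35 gave slope bias of about 0.1, calibration slope 0.85 to 1.28 and coverage 93.5 to 93.8%. In one of them, slope RMSE was 1.18 with full input, 1.24 with mean/mode input and 1.22 for a refitted reduced model. The reduced model had bias 0.00 and calibration slope 1.00.

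**The case against.** A reader might infer that the mean/mode rule is shown to give miscalibrated slopes and intervals that are too narrow. The documents do not support that. The errors need hidden-predictor-by-time effects, which are retained only if AIC favours them, and no coefficient is given. The direction is open too: a calibration slope of 1.28 rests on an assumed positive correlation, and a negative one puts it below 1.

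The errors may also be modest. In the 0.4-per-year case the reduced model lowers slope RMSE only from 1.24 to 1.22, or 0.02/1.24 = 1.6%. Predicted eGFR itself suffers less than the slope, because the entered eGFR corrects most of the level error. One simulation with hidden slope effects of 0.4 found a 5-year eGFR calibration slope of 1.00 to 1.05 and RMSE about 3 to 4% higher.

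A reader might further suppose that Eq. (2) does harm by absorbing the hidden predictors' baseline effects into the random intercept. It matters little. With SDs of 15 and 6 the weight is 225/(225 + 36) = 0.86. Adding a hidden-predictor variance of 25 gives 250/(250 + 36) = 0.87.

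Finally, the web tool is a secondary aim, the full model and clinician interface are untouched, and the article does not claim that the limited-input version was itself validated. One shared formula also keeps the two interfaces consistent.

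These arguments limit the size and certainty of the error. They do not remove the mean/mode rule or the lack of any test of it.

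**Conclusion.** The point holds in a conditional form. Two parts rest on the text alone: ten of 13 predictors are fixed at means or modes in the patient interface, and the planned validation never runs the model that way, although the tool is introduced as the externally validated model. Because the rule itself is stated, this is not detail that a condensed article has merely left out.

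The statistical consequences depend on hidden predictors having time effects. Under assumed effects of 0.4 per year, slope bias is about 0.1 per year in size (0.5 mL/min/1.73m² over five years), calibration slope about 0.85 to 1.3, and coverage about 93.5 to 94%. Stronger assumed effects bring slope-interval coverage to about 90%. Without such effects the error is close to zero. Neither size nor direction can be fixed from the documents, which is itself a reason to test this version.

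**What to change.** Drive the patient interface from a rule that matches its inputs, in one of two ways:

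- Fit a reduced mixed model on the same development data, with age, sex, UACR and their time interactions. Let baseline eGFR enter through Eqs. (2)–(4) using that model's own variance components.
- Keep the full model, but average over the hidden predictors given the entered ones, and add the resulting variance to the intervals and to Eq. (5).

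Put the chosen version through the same leave-one-country-out and DIACORE validation, with interval coverage added to the measures. At minimum, run the mean/mode version through that validation, and do not present it as externally validated until the results are in.

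No new data are needed. A reduced model costs one extra fit, one extra set of validation results and a second set of coefficients to publish. The two interfaces may also give the same patient different answers, which users should be told. The relative-risk output compares the patient with someone of the same age, sex and baseline eGFR who has the best values on everything else. Under a reduced model only UACR is left to vary, so in the patient interface that output must be redefined or dropped.
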